### **1. RATIONALE FOR THE STUDY**

It is well established that air pollution contributes to cardiovascular morbidity and mortality. Moreover, the American Heart Association recognizes that air pollution is a significant risk factor for cardiovascular disease. Particulate matter (PM) has been the major focus of previous acute air pollution studies. Less attention has been paid to acute cardiovascular responses to ozone (O3), at least in part due to the notion that O3 causes primarily local effects on the respiratory tract. However, several recent epidemiological studies reported increased risk of mortality associated with ambient exposure to O3.

The maximum level of ozone in ambient air is regulated by the U.S. Environmental Protection Agency (EPA) as part of its mandate to set a National Ambient Air Quality Standard (NAAQS) for pollutants considered to be harmful to public health and the environment. The ozone NAAQS has been established largely based on data from human clinical studies showing decrements in lung function at ozone exposure concentrations as low as 0.07 ppm for 6.6 hours with extensive exercise. In March 2008 the EPA lowered the 8-hour ozone NAAQS to 0.075 ppm (from 0.080 ppm). More recently the EPA administrator proposed a revision to the 8-hour standard, within the range of 0.060-0.070 ppm, based on these lung function effects. However, it is unknown whether there are acute cardiovascular effects at these same ozone exposure levels. General pathways by which air pollutants, including ozone could cause vascular dysfunction include a) the induction of systemic inflammation and/or oxidative stress and b) alterations in autonomic balance. These initial responses could lead ultimately to endothelial dysfunction, impaired arterial dilation, cardiac arrhythmias, and increased pro-thrombotic activity in circulating blood, which could present a risk to individuals with atherosclerotic arterial disease.

The epidemiologic associations between exposure to ozone and increased risk of cardiovascular disease have raised new concerns about potentially harmful cardiovascular effects of this pollutant and there is a need for additional data from controlled human clinical studies, without many of the limitations common in observational studies, to assess potential ozone-mediated cardiovascular health effects. While controlled human exposure data on acute cardiovascular responses to ambient PM exposure have been accumulating due to directed research funding to support the epidemiological evidence of a PM-mortality association, the available data from controlled human exposures regarding the cardiovascular effects of O3 are extremely limited. This study will address this data gap by investigating whether short-term controlled exposure to ambient levels of O3 causes acute cardiovascular responses as assessed by changes in blood pressure, cardiac function, and systemic biomarkers of inflammation, endothelial dysfunction, and thrombosis.

The protocol for this study is based on the following suppositions:

- Although spirometric responses to ozone are known to be attenuated in older individuals, the elderly may be more susceptible to inflammatory and systemic vascular effects of ozone exposure compared with younger people.
- Detectable effects at low levels of inhaled ozone are more likely with exercise (increased ventilation) during the exposure.
- Subjects with pre-existing CV disease should be excluded for safety and to minimize variability

The study will be conducted in three research centers using a common protocol and common standard operating procedures. The subjects to be studied are healthy non-smoking adults aged 55 to 70 years who meet strict criteria for inclusion. They will be exposed in a chamber to clean air and two concentrations of ozone (70 and 120 ppb) for 3 hours while exercising intermittently. The lower concentration was chosen because it is between the current ozone NAAQS and the new proposed NAAQS. The higher concentration is within the range of concentrations many people are still exposed to in the United States (<http://www.epa.gov/airquality/greenbook/oindex.html>). To carry out the study each center's team consists of a multi-disciplinary group with experience in pulmonary and cardiovascular medicine, occupational/environmental medicine, cardiology and controlled human exposure studies of ozone health effects. A Data Coordination and Analysis Center will be responsible for assembling all the data from the centers and conducting the statistical analyses of the combined data set.

## **2. HYPOTHESES**

### **Primary hypotheses**

We hypothesize that ozone reaction products in airways surface liquid interact with lung cells (e.g., epithelial cells, macrophages, nociceptive sensory nerve endings, endothelial cells), and that these cells produce mediators that enter the pulmonary and systemic vasculature. In addition to its (local) effects on airway inflammation and lung function, ozone may have the following cardiovascular effects:

- (1) altered autonomic balance (measured as changes in heart rate and heart rate variability (HRV)), cardiac arrhythmia, and repolarization
- (2) altered systemic vascular function [measured as brachial artery flow-mediated dilation (FMD) ~~without and with nitroglycerin (NTG)~~ – primary endpoint].
- (3) pro-thrombotic vascular state (measured as increase in von Willebrand factor antigen in blood – primary endpoint). Secondary endpoints are: increase in microparticle-associated Tissues Factor activity and platelet activation.

### **Secondary hypotheses**

We further hypothesize that:

- Markers of systemic oxidative stress and inflammation are correlated with the cardiovascular effects and degree of airway injury (measured as CC16 in blood) and airway inflammatory effects (neutrophils and cytokines in induced sputum).
- Cardiovascular effects are correlated with airway inflammatory effects.

### **Exploratory hypothesis**

Subjects with GSTM1 null genotype (with impaired antioxidant defenses) will be more susceptible to effects of ozone.

### 3. CRITERIA FOR INCLUSION AND EXCLUSION

#### Inclusion

- $\geq 55$  and  $\leq 70$  years of age; nonsmoking males and females of all ethnic backgrounds.
- Normal spirometry ( $FEV_1$  and FVC  $\geq 75\%$  of predicted and  $FEV_1/FVC \geq 0.65$ ). Predicted values will be determined using the correction factor specific for African Americans and Latinos, but not for Asians, based on the NHANES III guidelines.
- Ability to complete the training exercise regimen chosen to induce an inspired ventilation rate of 13.6 to 15.5 L/min/m^2 body surface area (BSA) ATP (Ambient Temperature, Pressure) which is equivalent to 15 to 17 L/min/m^2 BTPS (Body Temperature, Pressure saturated with water vapor) without exceeding 80% of predicted maximal heart rate.
- Normal baseline 12-lead resting ECG, and absence of significant ST depression while performing the 15-minute required level of exercise targeted for the exposure period.
- Subjects must be able to avoid the medications supplements listed in Table 1 of section #7 for 1 week before the exposure.

#### Exclusion

- Non-English speaking.
- Including, but not limited to as ascertained by the physicians: Subjects with chronic cardiovascular (such as ischemic heart disease) or respiratory (such as asthma or COPD) disease; diabetes, or other organ or system dysfunction; cerebrovascular disease; active psychiatric disorders that would interfere with the subject's ability to understand and participate in the study. Subjects who have tested positive for a disease that affects the immune system (such as HIV, lymphoma, leukemia) or current drug or alcohol abuse (defined as having more than 3 drinks per day or being unable to abstain from alcohol for 3 days). [Refer to the Initial Phone Screen Questionnaire for a detailed list.](#)
- Subjects with atopy or allergic rhinitis will not be excluded as long as they do not require regular treatment with antihistamines or systemic steroids.
- Ever-smokers (smoked tobacco or marijuana during the last five years, or with history of >10 pack year for tobacco or > 1 joint year for marijuana, or living with a smoker who smokes inside the house).
- Subject having plasma cotinine level > 3ng/mL.
- BMI >35 and <18 (35 is the official cut off for class 1 obesity).
- Hypertension (defined as blood pressure >140 systolic or >90 diastolic) or on anti-hypertension medications other than diuretics.
- Pregnancy or nursing (breastfeeding).
- On the following medications: prednisone, statins, beta-blockers, anticoagulants, current systemic estrogen therapy, tamoxifen. Subjects will not be asked to discontinue needed prescription medications for the purpose of this study. If any of these medications becomes necessary during the course of the study, the subjects will be excluded. Use of other medications will be considered on an individual basis (see section # 7).

- Subjects taking aspirin or PDE5 inhibitors must be willing to abstain from these medications during the week preceding each exposure (see section #7).
- Occupational exposures (exposed to high levels of vapors, dust, gases, or fumes on an on-going basis)

#### **4. SUBJECT RECRUITMENT, INFORMED CONSENT, AND CONFIDENTIALITY**

Subjects will be recruited by advertisement on local bulletin boards, by advertisement in local newspapers, in publications oriented to the required age group, and on Craigslist, notices placed in retirement complexes, and by recruitment from clinics at the investigator's institutions. Word-of-mouth contacts by previous subjects will be solicited. The initial screening will be done by phone.

Number of subjects in each center: n=30 (who have completed all three exposure sessions). Approximately 140 subjects in total would be recruited to achieve the target number of subjects completing the three exposure sessions.

##### Informed Consent

During the screening visit 1 (see below), the investigator will obtain all informed consents from the study subject by means of a dated and signed consent approved by the local IRB/EC. The study subject will be given a copy of all signed informed consent forms. The informed consent process will be performed in accordance with the International Conference on Harmonization guidelines for Good Clinical Practice (GCP) and federal laws and regulations.

##### Subject confidentiality

Patient confidentiality will be maintained according to ICH guidelines for GCP and applicable local and national data protection laws. A study identification number will be assigned to each subject. The link between patient identifiable information and I.D. number will be stored only at the clinical center where the subject receives his/her care, thereby ensuring that all data transferred from a subject's medical records to a study report form and any process derived from the study report form is handled confidentially.

#### **5. SCREENING AND TRAINING VISITS**

Subjects who volunteer to participate will visit the laboratory or clinical research center (CRC) for screening and training on two separate days.

##### **Screening visit – Visit #1 (baseline subject characterization and questionnaires)**

A *Health and Home Screening Questionnaire*, and a physical examination, will be administered to obtain the following: medical history, cardiovascular and respiratory health status, occupational history, history of allergies, use of medications and vitamin supplements, diet, alcohol use, occupational exposure, SES, home characteristics/heating type and air conditioning use. Particular attention will be given to medical history or physical findings suggesting arterial vascular or cardiac disease, or unexplained syncope or unusual dyspnea as well as other risk factors for cardio-vascular disease. Height, weight, and vital signs will be measured. In a woman who has not yet completed menopause, a urine pregnancy test will be done.

A baseline 12-lead ECG will be taken at rest. Trained personnel will be responsible for attaching the leads. If the instrument interpretation is normal, the ECG will be reviewed and signed by the study

physician. If any abnormalities are detected, it will be reviewed by the cardiologist. In consultation with the cardiologist, the local study physician will make the decision whether the subject should be included.

Spirometry will be performed on a spirometer that meets American Thoracic Society performance criteria using NHANES III predicted values.

Venous blood will be collected for analyses of cotinine (markers of exposure to tobacco smoke), total and differential blood counts, metabolic profile, and lipid profile (cholesterol, HDL, and triglycerides).

### Training visit – Visit #2

Vital signs will be measured. In a woman who has not yet completed menopause, a urine pregnancy test will be done. The subject will exercise (on a treadmill or a stationary bicycle) for 15 minutes, rest for 15 minutes, and exercise another 15 minutes. The level of exercise will be adjusted to achieve the target inspired minute ventilation ( $V_i$ ) of 13.6 to 15.5 L/min/m^2 BSA (ATP) which is equivalent to target expired minute ventilation ( $V_E$ ) of 15 to 17 L/min/m^2 BSA (BTSP) assuming the correction factor of 1.1 (the same that will be required during the exposure period), measured by a mouthpiece and pneumotachograph, while not exceeding 80% of the predicted maximum heart rate (HR). 80% of the predicted maximum heart rate per minute will be calculated from the following formula  $HR_{max} = 208 - 0.7 \times \text{age (yrs)}$  (Tanaka et al, J Am Coll Cardiol 37:153, 2001). For example, a 70-year old subject would have a maximum predicted heart rate of 159 beats/min and the exercise required to achieve a minute ventilation of at least 13.6 L/min/m^2 BSA (ATP) in that subject must not cause the heart rate to exceed 127 beats/min.

Blood pressure will be measured at rest pre- and post-exercise and possibly during exercise if sudden changes in HR are observed. 3-lead cardiac monitoring will be performed during the 45-minute exercise/rest/exercise period. A rhythm strip printout will be obtained before the exercise and every 5 minutes during the exercise. Trained personnel will be responsible for attaching the leads and a physician will be present for the first 15-minute exercise period, and in the building, reachable by pager, during the rest of the visit. The cardiac rate and rhythm will be monitored in real time by the study personnel and by the physician while present during the first exercise period. The monitor's printout will be reviewed and signed by the study physician; if the subject can also complete the level of exercise needed, the subject would be entered into the study. If any abnormalities such as ST depression, arrhythmias, or other abnormalities, are detected, they will trigger a review by the cardiologist. In consultation with the cardiologist, the local study physician will make the decision whether the subject should be included. An *Ozone Monitor Activity Diary* and a personal exposure sampler (PES) will be given to the subject with instructions for filling the diary and wearing the PES. The sampler should be worn for the 3 days preceding the pre-exposure day (starting at noon).

## 6. EXPOSURE VISITS AND TIMELINE OF MEASUREMENTS

Subjects will be exposed to clean air, 70 ppb (low), and 120 ppb (high) ozone for 3 hours in a randomized order. Each exposure session involves 3 consecutive days as shown below. There will be a minimum 2-week period between the exposure sessions.

| Exposure (order will be randomized) | Pre-exposure day | Exposure day | Post-exposure day |
|-------------------------------------|------------------|--------------|-------------------|
| Clean Air                           | Visit 3          | Visit 4      | Visit 5           |
| 70 ppb ozone                        | Visit 6          | Visit 7      | Visit 8           |

|               |         |          |          |
|---------------|---------|----------|----------|
| 120 ppb ozone | Visit 9 | Visit 10 | Visit 11 |
|---------------|---------|----------|----------|

**Prior to visit 3, 6, and 9** the subjects will receive reminder phone calls and will be asked to answer the *Before Pre-exposure Visit Phone Questionnaire*, which includes questions about the subject's health and medication use and gives a few reminders about the upcoming visit or, if necessary, provides the opportunity to reschedule the visit.

**Visit 3, 6, and 9 - pre-exposure day.** The subject will arrive at the laboratory or CRC at 11:30 am –12:00 noon. A low-fat lunch (25-30% fat) will be provided. The *Ozone Monitor Activity Diary* and PES will be collected and the subject will answer *Pre-Exposure Day Health Questionnaire*. In a woman who has not yet completed menopause, a urine pregnancy test will be done.

The following procedures will be carried out: measurement of vital signs, venous blood draw (up to 30 mL), ultrasound measurement of flow-mediated (FMD) and ~~nitroglycerin-mediated (NTG)~~ brachial artery dilation ultrasound (BAU). A box dinner will be provided. The subject will spend the night at the CRC or at a nearby hotel. Before discharge the subjects will be reminded that the researchers believe it is important to avoid any environmental exposure that might possibly affect his/her reaction to the controlled exposure scheduled for the following morning. For that reason they are providing a boxed supper and close-by sleeping accommodation in a nonsmoking environment. They will stress that the subject's thoughtfulness and cooperation is very much appreciated.

**Visit 4, 7, and 10 – exposure day.** The subject will arrive at the laboratory or CRC at 7:00 – 7:30 am. A regular breakfast will be provided. The following events will occur: blood pressure (and other vital signs) will be measured; the subject will complete the symptom questionnaire; the subject will wear a Holter monitor, heart rate variability (HRV) will be measured (the subject lies quietly for 5 minutes then the ECG is recorded for 5 minutes under tidal breathing) and continuous ECG recording will begin; spirometry will be measured.

The exposure will start between 8:00 and 8:30 am and will last 3 hours. The subject will alternate a 15-minute exercise period with a 15-minute rest period. Subjects will be blinded to ozone dose and order of exposure. Assignment of each subject to the exposures will be randomized (see Section #15).

Minute ventilation will be measured with pneumotachograph between 8 and 10 minutes of the first exercise period and during the last 2 minutes of the first, second, fourth, and sixth exercise period and the exercise load adjusted as needed. Blood pressure will be measured during a rest period, 5 minutes before the first, third and fifth exercise period. Heart rate will be measured twice during the first exercise period and once during each of the other exercise periods.

The symptom questionnaire will be filled out by the subject in the chamber during the last 15 minutes of exposure. Immediately after exposure blood pressure (and other vital signs) will be measured, then HRV and spirometry. A low-fat (25-30% fat) lunch will be provided.

Approximately 3.5 hours after the end of the exposure the sequence of the measurement will be: HRV, venous blood draw (up to 30 mL), BAU FMD and ~~NTG-mediated dilation~~, symptom questionnaire, and blood pressure (and vital signs). The subject will be sent home wearing the Holter monitor. The subject will leave the laboratory or CRC at around 4:00 pm.

**Visit 5, 8, and 11 –post-exposure day.** The subject will arrive at the laboratory or CRC at 8:00 am. The subject will need to be fasting from 7:30 am 2 hours prior to sputum induction, in order to avoid contamination of the sputum specimen. The sequence of measurements will be: vital signs, symptom questionnaire, HRV, venous blood draw (up to 30 mL), and spirometry/sputum. Blood pressure may be measured. The subject will leave the laboratory and CRC at around 10:30 am and will be given the *Ozone Monitor Activity Diary* and PES (and associated instructions) to wear before the next exposure visit (with exception of visit 11).

## **7. ACTIVITY, DIET, AND OTHER REQUIREMENTS ON DAY(S) PRIOR TO EXPOSURE**

Subjects should abstain from caffeinated beverages (i.e., coffee, tea, energy drinks, and sodas) and alcoholic beverages starting with lunch the day before the exposure through the post-exposure day. Subjects must be able to avoid the medications and supplements listed in Table 1 below for 1 week prior to the exposure. In addition, subjects will not be studied within 6 weeks of a respiratory infection. Use of diuretics to control mild hypertension will be permitted.

Subjects will wear the PES for the 3 days, starting at noon, before the pre-exposure day. Subjects will be asked to abstain from exercising on the day before the exposure. They will fill out the *Ozone Monitor Activity Diary* while wearing PES.

Table 1

| For one WEEK before each exposure day                                      |
|----------------------------------------------------------------------------|
| Non-steroidal anti-inflammatory drugs such as ibuprofen, naproxen, aspirin |
| Phosphodiesterase 5 (PED5) inhibitors such as Viagra, Cialis, Levitra      |
| Supplemental vitamins                                                      |
| Antihistamines                                                             |
| Anti-oxidants                                                              |
| Fish oil                                                                   |
| Niacin                                                                     |
| Arginine                                                                   |
| Over-the counter decongestants                                             |

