## **8. CARDIOVASCULAR AND PULMONARY OUTCOMES**

The majority of the endpoints will be measured on the day before the exposure and at 4 and 22 hours after the exposure. Markers of inflammation in sputum will be measured only once because sputum will be induced only at 22 hours after the exposure.

**Health symptoms.** These will be assessed using a symptom questionnaire.

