#### Data Safety Monitoring Plan

Adverse events will be graded according to the following scale:

Grade 1 Mild: transient mild discomfort; no limitation activity; no medical intervention or therapy required.

Grade 2 Moderate: mild to moderate limitation in activity, some assistance may be needed; **minimal noninvasive intervention or therapy (such as over-the-counter medication, application of ice, etc.) is allowed.** ~~no medical intervention or therapy required.~~

Grade 3 Severe: marked limitation in activity; some assistance required; medical intervention or therapy required, hospitalization possible.

Grade 4 Life-threatening: extreme limitation in activity, significant assistance required; significant medical intervention or therapy required; hospitalization probable.

Subjects will be encouraged to contact us if any adverse effects are noted after visits to the laboratories. They will have a 24-hour contact and pager numbers to report any potential adverse events that occur after study visits. If any subject has more than mild adverse effects from participation in the protocol or if several subjects have mild adverse effects, we will consider changing the protocol to improve subject safety and comfort. All adverse events that occur during the course of the study will be reported to the relevant IRB in accordance with current institutional guidelines. Subjects with two or more Grade 3 adverse events or with one Grade 4 adverse event will be withdrawn from the study. Information on adverse events will also be collected on a standardized data form and submitted to the Advance Data Entry and Protocol Tracking (ADEPT) system (at the Data Coordinating and Analysis Center) within 5 working days of occurrence (or as soon as the center is notified of the occurrence), with the exception of grade 3 and 4 events, which will be reported within 24 hour of occurrence (or as soon as the center is notified of the occurrence). The Data Coordinating and Analysis Center will periodically generate a report of all adverse events and submit it to the Steering Committee, the DMB, and HEI. As soon as the occurrence of a grade 3 or 4 event is reported to the ADEPT system, the Steering Committee and HEI will

be notified via email and the aggregated Adverse Events report will be generated and become available for viewing.

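### The Table 1 product and exercise restrictions end before the 22-hour measurements, unlike the caffeine and alcohol restriction, and no product use is recorded in between

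*Protocol*

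**What the plan says.** The window for Table 1 products (NSAIDs including aspirin, PDE5 inhibitors, vitamins, antihistamines, antioxidants, fish oil, niacin, arginine, decongestants) is stated four times in the Protocol:

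- Section 3, Inclusion: products "listed in Table 1 of section #7 for 1 week before the exposure".
- Section 3, Exclusion: aspirin and PDE5 inhibitor users must be willing to "abstain from these medications during the week preceding each exposure".
- Section 7, text: "Subjects must be able to avoid the medications and supplements listed in Table 1 below for 1 week prior to the exposure".
- Section 7, Table 1 heading: "For one WEEK before each exposure day".

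Section 7 also asks subjects not to exercise on the day before exposure. It names no other day. For caffeine, and in the same sentence for alcohol, it sets a longer window: "alcoholic beverages starting with lunch the day before the exposure through the post-exposure day".

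Section 8 places most endpoints on the day before exposure and "at 4 and 22 hours after the exposure", with sputum at 22 hours only. Section 14 makes both the 4-hour and the 22-hour values dependent variables of the primary model, with the pre-exposure value as covariate. Section 6 describes a telephone questionnaire that covers medication use before visits 3, 6 and 9. Its list for visits 5, 8 and 11 has vital signs, symptoms, HRV, blood, spirometry and sputum, but no medication question.

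**The concern.** One paragraph of section 7 carries one restriction across the 22-hour measurements and lets the others lapse, without giving a reason. A subject who follows the stated windows exactly can have a baseline measured off a product and a 22-hour value measured on it. Aspirin users are a concrete case: they are admitted if they abstain for the preceding week, and nothing in the text says when that abstinence ends.

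The 22-hour outcomes at stake include vWF, platelet activation, CRP, IL-6, 8-isoprostane, HRV and sputum cells and cytokines. Sputum has no earlier value in the session to fall back on. Because no question about use is listed at the post-exposure visit, the analyst would have no planned way to identify affected values. The next medication question comes before the following session, at least two weeks later, and after the third session none is listed.

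**Working it through.** **Step 1: do the measurements fall after an unsupervised interval?** Inputs are the clock times in section 6.

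- Exposure starts 8:00-8:30 and lasts 3 h, so it ends 11:00-11:30.
- 4-hour values: 11:00-11:30 + 4 h = 15:00-15:30, before discharge at about 16:00.
- 22-hour values: 11:00-11:30 + 22 h = 9:00-9:30 next day, inside the visit that runs from 8:00 to about 10:30.
- At home: about 16:00 to 8:00 = 16 h, and 16/22 = 73% of the interval.

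**Step 2: which outcomes are reached?**

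| Outcome | About 4 h, before discharge | About 22 h, after the night at home |
|---|---|---|
| FMD (primary) | measured | not scheduled |
| vWF (primary) and other blood markers | measured | measured |
| HRV | measured | measured |
| Sputum | not scheduled | measured (only time) |

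Only the right-hand column is open to use at home.

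**Step 3: how could use affect the ozone contrast?** Let d be the product's effect on the marker, and let p1 and p0 be the proportions using it after ozone and after clean air.

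- Equal use, additive effect: the mean shift is (p1 − p0) × d = 0. The cost is added variance.
- Equal use p, with the product removing a fraction b of the ozone response: the contrast becomes (1 − p × b) times its true size. The crossover does not cancel this.
- Unequal use: bias = (p1 − p0) × d. Subjects are blinded and order is randomized, so this needs a route such as symptoms.

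**Step 4: illustration of the unequal-use case.** The Protocol gives no SD, effect size or usage rate, so every usage and effect input below is an assumption. Effects are in SD units of the within-subject difference.

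- Standard error with 90 completers: 1/√90 = 0.105 SD.
- Low end: 0.02 × 0.3 = 0.006 SD, and 0.006/0.105 = 6% of one standard error.
- Middle range: 0.05 × 0.3 = 0.015 SD (14%) to 0.15 × 0.5 = 0.075 SD (71%).
- High end: 0.20 × 0.5 = 0.10 SD (95%).

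The range is wide because it depends almost wholly on the assumed difference in use, on which the Protocol has no data.

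**The case against.** The strongest objection concerns the link to ozone level. A reader might infer that the Protocol expects ozone to cause chest symptoms and so drive medication use. It does not. Section 16 says that ozone can do so in responders, and then that these exposures are unlikely to, especially in older adults. Nor does the Grade 2 definition in section 13 ("minimal noninvasive intervention or therapy (such as over-the-counter medication, application of ice, etc.) is allowed") predict treatment after ozone: it is a severity scale for any adverse event. This objection stands. Ozone-dependent use is possible, but the documents do not show it to be likely.

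A second objection is that a longer restriction would not close the symptom route if symptom treatment stays open, as it must. That also stands. Aligning the windows deals mainly with habitual use; only recording deals with symptom-driven use.

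Third, the symptom questionnaire and the adverse event form may capture some use, and section 1 mentions common standard operating procedures that are not shown. These might narrow the gap. They do not change what sections 3, 6 and 7 say.

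Fourth, section 7 gives no reason for the Table 1 or the caffeine rule. That the Table 1 products were barred because they alter the outcomes is an inference, so the point rests on the mismatch between the windows and the measurement times.

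**Conclusion.** The point holds for the 22-hour outcomes. Sections 3 and 7 end the Table 1 restriction at exposure and name only the day before for exercise, while the caffeine and alcohol restriction covers the post-exposure day. About 16 hours at home precede values that enter the primary model, and no question about use is listed.

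The consequence is possible noise, possible blunting of a response and, if symptoms prompt use, possible bias by ozone level. The size is unknown and probably modest; the range of 0.006 to 0.10 SD is illustrative and rests on assumed inputs.

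Two stronger conclusions are not supported. Both primary endpoints are not at risk: FMD and the 4-hour vWF precede discharge. The open interval is also not the full span from arrival on the exposure morning, because until about 4 pm the subject is on site. It is worth correcting because the change is small and the affected values could not be identified afterwards.

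**What to change.** - **Sections 3 and 7, including the Table 1 heading:** reconcile the Table 1 and exercise windows with the 22-hour measurement schedule, as section 7 already does for caffeine and alcohol, and use the same wording in all four places. Leave treatment of symptoms and prescribed products to the investigators.
- **Section 6, visits 5, 8 and 11:** ask about and record any Table 1 product or exercise since the exposure, with the time. This restricts nothing and is useful whatever window is chosen.
- **Analysis:** keep all values in the primary analysis and repeat the 22-hour analyses without the affected values. This should remain a sensitivity analysis, because use after exposure may itself be a consequence of exposure and excluding on it could introduce selection.

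Cost: about one more day of restriction per session for discretionary products and exercise, one added question at three visits, and some flagged values. For sputum, dropping a flagged value loses that session's only measurement.
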